### **3.7 Stopping rules for the study**

The study will be stopped if at least 1 patient experiences a severe adverse event that is attributable to lanadelumab treatment and evaluation will take place before the next subject is treated or whether the second dose of lanadelumab can be given. A semi-sequential design will be deployed. This means that we will start with a single individual to be entered into the study. A second subject can enter the study 24 hours after the first subject has started. After the second participant has received the first dose without severe complications, the 3rd to 5th participant may be recruited.

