### 4.1 Dose rationale and rate of infusion

We refer to the attachment with the results from the modeling and simulation data. This provides the necessary rationale to administer 300 mg IV followed by a second dose of 300 mg IV on day 4 of treatment.

Lanadelumab will be administered in a similar way as all current monoclonal antibodies are given. That is a ramp up scheme in which the infusion rate is steadily increased. For lanadelumab we will follow the following scheme. In the end the total volume will be administered over a period of 1 hour.

| Dose                           | duration   | Rate                      |
|--------------------------------|------------|---------------------------|
| First 30 mg = 10 mL            | 20 minutes | 30 mL/hour = 90 mg/hour   |
| 30-100 mg (70 mg) = 23.33 mL   | 20 minutes | 70 mL/hour = 210 mg/hour  |
| 100-300 mg (200 mg) = 66.67 mL | 20 minutes | 200 mL/hour = 600 mg/hour |

300 mg is diluted in 100 mL NaCl 0.9% to a concentration of 3 mg/mL

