### Data and outcome variables:

Data on clinical parameters including respiratory rate, oxygen saturation, and supplemental oxygen are registered before and after administration of lanadelumab and then daily. Changes in oxygen support requirement and clinical symptoms are recorded. Laboratory tests are performed during the study: hemocytometry, WBC differentiation, D-dimer, ferritin, CRP, and albumin (Table 1).

Kinins, biomarkers, and functional immunological profiling will be assessed in the forty randomized patients with EDTA plasma (10ml), PBMCs (20ml EDTA), mass spectrometry (2ml blood in specialized medium tube), and citrate plasma (8ml), with a total volume of 40ml per in depth sampling.

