#### ***Adverse events (AEs)***

Adverse events are defined as any undesirable experience occurring to a subject during the study, whether or not considered related to the investigational product. All adverse events reported spontaneously by the subject or observed by the investigator or his staff will be recorded, meeting all of the following criteria:

- **Severity: Grade 2 or higher, or grade 1 lasting longer than 1 week, graded by the CTCAE (Common Terminology Criteria for Adverse Events, v5.0).**
- **Causality: there needs to be a reasonable suspicion of the AE being an effect of the study medication.**

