#### ***Serious Adverse events (SAEs)***

A serious adverse event is any untoward medical occurrence or effect that

- results in death;
- is life threatening (at the time of the event);
- requires hospitalisation or prolongation of existing inpatients' hospitalisation, admittance to the Intensive Care Unit due to respiratory insufficiency will not be reported as an SAE;
- results in persistent or significant disability or incapacity;
- is a congenital anomaly or birth defect; or
- any other important medical event that did not result in any of the outcomes listed above due to medical or surgical intervention but could have been based upon appropriate judgement by the investigator.

The investigator in a participating center will report all SAEs to the coordinating investigator without undue delay after obtaining knowledge of the events.

The sponsor will report the SAEs through the web portal *ToetsingOnline* to the accredited METC that approved the protocol, within 7 days of first knowledge for SAEs that result in death or are life threatening followed by a period of maximum of 8 days to complete the initial preliminary report. All other SAEs will be reported within a period of maximum 15 days after the sponsor has first knowledge of the serious adverse events.

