***Suspected unexpected serious adverse reactions (SUSARs)***

Adverse reactions are all untoward and unintended responses to an investigational product related to any dose administered.

Unexpected adverse reactions are SUSARs if the following three conditions are met:

1. the event must be serious;
2. there must be a certain degree of probability that the event is a harmful and an undesirable reaction to the medicinal product under investigation, regardless of the administered dose;
3. the adverse reaction must be unexpected, that is to say, the nature and severity of the adverse reaction are not in agreement with the product information as recorded in:
  - Summary of Product Characteristics (SPC) for an authorised medicinal product;
  - Investigator's Brochure for an unauthorised medicinal product.

The investigator in a participating centre will report the SUSAR to the coordinating investigator.

The coordinating investigator will report expedited the following SUSARs through the web portal *ToetsingOnline* to the METC:

- SUSARs that have arisen in the clinical trial that was assessed by the METC;
- SUSARs that have arisen in other clinical trials of the same sponsor and with the same medicinal product, and that could have consequences for the safety of the subjects involved in the clinical trial that was assessed by the METC.

The remaining SUSARs are recorded in an overview list (line-listing) that will be submitted once every half year to the METC. This line-listing provides an overview of all SUSARs from the study medicine, accompanied by a brief report highlighting the main points of concern.

The expedited reporting of SUSARs through the web portal Eudravigilance or ToetsingOnline is sufficient as notification to the competent authority.

The sponsor will report expedited all SUSARs to the competent authorities in other Member States, according to the requirements of the Member States.

The expedited reporting will occur not later than 15 days after the sponsor has first knowledge of the adverse reactions. For fatal or life threatening cases the term will be maximal 7 days for a preliminary report with another 8 days for completion of the report.

**For individual sites, the local investigator completes the SAE report in Castor and providing as much detailed information as known and relevant to the event within 24 hours of discovery of the event.**

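### Section 3.7 sets no observation time after the second participant's first dose, and counts subjects rather than lanadelumab recipients, before releasing three more

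*Protocol*

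**What the plan says.** Section 3.7 contains a single-event stop and a staggered start. On an attributable severe adverse event the study stops, and "evaluation will take place before the next subject is treated or whether the second dose of lanadelumab can be given". The stagger has two release steps:

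- **First step (participant 1 to participant 2).** "A second subject can enter the study 24 hours after the first subject has started".
- **Second step (participant 2 to participants 3 to 5).** Recruitment of the next three opens "After the second participant has received the first dose without severe complications".

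The second step states no number of hours and names no one to confirm that its condition is met. Both steps are counted in subjects or participants. Section 5.3 allocates them 1:1 to lanadelumab or standard management through Castor, immediately on entry, and gives each site drug for at least one patient.

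Section 4.1 describes the infusion: "In the end the total volume will be administered over a period of 1 hour". Section 6.1 (Data and outcome variables) says that clinical parameters "are registered before and after administration of lanadelumab and then daily".

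**The concern.** The stagger is the protocol's own safeguard for a new route. Section 1.2 says that intravenous dosing was not tested in the HAE clinical package, Section 2 chooses to go straight into patients rather than healthy volunteers, and Section 1.3 makes safety of the intravenous route a primary objective. The 24 hours at the first step show that the authors wanted time to watch a patient after the infusion.

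That time is missing at the second step, where release goes from one patient to three. A reaction that appears some hours after participant 2's infusion could come after the next three have been released, and the stopping rule can act only on an event that is already known.

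The unit of counting is a second weakness in the same rule. If a subject is any randomised patient, participant 1 may be a control, and the first wait then observes no intravenous exposure. If participant 2 is a control, there is no first dose on which the second step can turn.

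**Working it through.** **Inputs.** Wait at the first step: 24 h from participant 1's start (Section 3.7). Wait at the second step: none stated (Section 3.7). Infusion volumes and rates: Section 4.1. Allocation: 1:1 without stratification (Section 5.3). Study length: one month (Section 3.4) or 12 months (synopsis). Assumption: simple randomisation, since the protocol does not describe the allocation algorithm.

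**1. Infusion time, reproduced.** Time = volume / rate, summed over the three steps: 10/30 + 23.33/70 + 66.67/200 h = 20 + 20 + 20 min = 60 min. This agrees with the stated 1 hour.

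**2. Observation required after the end of infusion.**
- First step: 24 h − 1 h = 23 h, if participant 1 received lanadelumab.
- Second step: 0 h. The text is satisfied as soon as the dose is in and no severe complication has occurred.

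**3. Effect of counting randomised patients.** With independent 1:1 allocation, each combination for the first two participants has probability 0.5 × 0.5 = 25%.

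| Participant 1 | Participant 2 | Probability | First step | Second step |
|---|---|---|---|---|
| Lanadelumab | Lanadelumab | 25% | 23 h after infusion | 0 h required |
| Control | Lanadelumab | 25% | no exposure observed | 0 h required, one patient exposed so far |
| Lanadelumab | Control | 25% | 23 h after infusion | condition cannot be met as worded |
| Control | Control | 25% | no exposure observed | condition cannot be met as worded |

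Participant 1 is a control with probability 50%, and so is participant 2. At least one of them is a control with probability 1 − 0.25 = 75%.

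**4. Exposure released at the second step.** On the randomised reading, 3 × 0.5 = 1.5 of participants 3 to 5 are expected to receive lanadelumab. The chance of at least one is 1 − 0.5³ = 87.5%, and of all three 0.5³ = 12.5%. If participant means lanadelumab recipient, all three receive it. These figures describe allocation, not the risk of a reaction, for which the protocol gives no intravenous rate in humans.

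**5. Time cost of using the same 24 h at both steps.** At present the second step can open 1 h after participant 2's infusion starts. With the change it opens at 24 h, so the added wait is 24 − 1 = 23 h. As a share of the study this is 23/720 = 3.2% of a 30-day month, or 23/8760 = 0.3% of 12 months. To reach two lanadelumab recipients, 2/0.5 = 4 randomised patients are needed on average instead of 2.

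**The case against.** The strongest reply is that a reaction would be noticed anyway. Section 5.5 has study personnel supervise dosing. The synopsis describes visits by doctor and nurse several times a day. Section 6.1 registers parameters after administration as well as before. The second step is also an affirmative condition: whoever recruits must have learned that participant 2's dose was given and tolerated, so silence from another site does not open it. Consent, eligibility testing and pre-dose sampling come before any further infusion, so 0 h is a floor for recruitment, not for dosing. If participant 2 is a control, the literal condition is simply unmet, which errs on the safe side.

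Most of this stands and limits the consequence. It does not supply an interval, and it does not help at the first step, where a control lets participant 2 enter with nobody yet exposed.

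Three stronger readings are tempting and are not supported:

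- *That the second step can open before any scheduled observation of participant 2.* The sentence that sets daily registration also requires registration after administration, and inpatients are seen more often than daily.
- *That a severe but non-serious reaction would escape, because Section 3.7 speaks of severe events and the reporting rules in Section 6.3 of serious ones.* Section 3.7 is itself a duty to stop on a severe event. A severe infusion reaction in patients this ill would usually meet a seriousness criterion, and "The investigator in a participating center will report all SAEs to the coordinating investigator without undue delay after obtaining knowledge of the events". The 24 hours for the Castor report is an outer limit for completing it, not leave to wait.
- *That nothing but modelling supports intravenous safety, as one sentence of Section 9.1.4 suggests.* Section 4.3 reports two intravenous studies in monkeys at up to 50 mg/kg without adverse findings. Cmax at that dose was 1010 to 1650 µg/mL, against 94.1 µg/mL predicted in humans after one 300 mg dose (Section 1.2). What is absent is human intravenous experience.

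**Conclusion.** The point holds as a weakness in how the stagger is written. Required observation after the end of the first infusion is about 23 h at the first step and 0 h at the second, and neither step is tied to a patient who has received lanadelumab. The residual exposure is narrow: a delayed post-infusion reaction in participant 2 at the move from one patient to three, or an early release with less intravenous exposure behind it than the stagger implies. Harm is made less likely by inpatient care, supervised ramp-up dosing and the single-event stop, but none of these sets an interval.

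The 50% and 75% figures rest on simple randomisation and on reading participant as randomised patient. On the other reading the counting problem disappears and the missing interval remains. A release rule of this kind belongs in the protocol and cannot be left to the SAP. It should be corrected, though it does not call the design as a whole into question.

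A reader might also infer that the first step is too short because its 24 h run from the start and not from the end of the infusion. The documents give no basis for preferring that extra hour.

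**What to change.** Amend Section 3.7 in three respects:

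1. Define both steps on lanadelumab-treated participants. A control neither opens a step nor triggers a wait.
2. Apply the protocol's own 24 hours, counted from the start of the first infusion, at the second step as at the first.
3. Open the second step only after the treating site has confirmed to the coordinating investigator that no severe event has occurred in the second lanadelumab recipient.

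Suggested wording: *The second lanadelumab recipient may be entered 24 hours after the start of the first recipient's first infusion. The third to fifth may be entered 24 hours after the start of the second recipient's first infusion, once the treating site has confirmed to the coordinating investigator that no severe event has occurred. Patients allocated to control do not count towards these steps.*

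The cost is about 23 hours of added waiting at the second step, less in practice because consent and screening already take time; one or two confirmations; and a longer lead-in when early patients are allocated to control (four randomised on average to reach two recipients). The text is short, but because it touches safety and conduct it may count as substantial under Section 10.3, and Section 9.2.1 requires approval before it takes effect. No separate notification system is needed.

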## 4. Treatment

In the current study subjects will be treated with lanadelumab 300 mg IV on day 1 followed by a second dose of lanadelumab 300mg IV on day 4.

### 4.1 Dose rationale and rate of infusion

We refer to the attachment with the results from the modeling and simulation data. This provides the necessary rationale to administer 300 mg IV followed by a second dose of 300 mg IV on day 4 of treatment.

Lanadelumab will be administered in a similar way as all current monoclonal antibodies are given. That is a ramp up scheme in which the infusion rate is steadily increased. For lanadelumab we will follow the following scheme. In the end the total volume will be administered over a period of 1 hour.

| Dose                           | duration   | Rate                      |
|--------------------------------|------------|---------------------------|
| First 30 mg = 10 mL            | 20 minutes | 30 mL/hour = 90 mg/hour   |
| 30-100 mg (70 mg) = 23.33 mL   | 20 minutes | 70 mL/hour = 210 mg/hour  |
| 100-300 mg (200 mg) = 66.67 mL | 20 minutes | 200 mL/hour = 600 mg/hour |

300 mg is diluted in 100 mL NaCl 0.9% to a concentration of 3 mg/mL

### 4.2 Drug interactions

Drug interactions are not expected for monoclonal antibodies as is confirmed by the details in the EPAR of lanadelumab.

### 4.3 Safety and potential risks

For general safety information we refer to the SmPC of lanadelumab.

Briefly stated it has the following information:

Hypersensitivity is an important identified risk and is discussed in the warnings and precautions of the reference labelling. In case of a severe hypersensitivity reaction, administration of TAKHZYRO must be stopped immediately and appropriate treatment must be initiated.

Immunogenicity is an important potential risk for lanadelumab and is monitored closely. The known potential risks of disordered coagulation associated with monoclonal antibodies have been characterized and no unexpected signals were identified.

The most commonly occurring adverse events with greater frequency in the lanadelumab treatment groups were injection site reactions (34.1% placebo, 52.4% lanadelumab) and dizziness (0% placebo, 6.0% lanadelumab). Less common reactions in the lanadelumab group compared to placebo include hypersensitivity (1% vs. 0%), increased liver enzymes (2% compared to 0%). An open-label extension study to evaluate the long-term safety and efficacy of lanadelumab for prevention of HAE attacks is ongoing. (Riedl et al., 2017). Pharmacokinetic analyses showed that the use of concomitant medications such as analgesic, antibacterial, antihistamine, anti-inflammatory, and antirheumatic medications used in the treatment of HAE had no effect on the pharmacokinetic properties of lanadelumab, suggesting that the drug-drug interaction potential of those evaluated drug classes is low. Similar observations were made for rescue medications, including plasma-derived and recombinant C1-INH, ecallantide, and icatibant, used for acute treatment of HAE attacks.

In this study two dosages of 300 mg intravenous lanadelumab are given on day 1 and day 4. The cumulative dose of 600 mg per week is higher than the current licensed dose for prevention of HAE. Even with a second dose given on day 4 of treatment the predicted drug concentrations remain far below the maximal tolerable dose. [see pop-PKPD modeling file with simulations]. We do not expect additional toxicity of the approach chosen.

Additional safety information to support for lanadelumab given as intravenous administration

Lanadelumab is currently marketed under TAKHZYRO tradename as a sterile, preservative-free, clear to slightly opalescent, colorless to slightly yellow solution currently approved in a single-dose glass vial for subcutaneous (SC) injection only; Injection: 300 mg/2 mL (150 mg/mL) solution. The Sponsor intends to use currently approved TAKHZYRO vials to be diluted in 100 mL saline solution bags for IV administration (Luo et al, 2020). Information on biostability after dilution is provided in the document "DX2930 Matl Compatibility and Cond of Use Stability Summary IV Tox MD 04AUG2014".

Based on the mechanism of action, PK/PD extrapolations, prior experience with lanadelumab in clinical trials, and supported safety profile based on the existing clinical package, the recommended dose is one infusion of lanadelumab 300 mg IV and a second dose of lanadelumab 300mg IV on day 4 (see pop-PKPD modeling and simulation file).

Preclinical safety information data after intravenous administration: (DATA ON FILE OF TAKEDA)

In addition to toxicology studies conducted via subcutaneous administration, lanadelumab was also evaluated in a single-dose IV infusion dose-range finding study with 4 weeks of recovery and a 4-week IV infusion study with 4 weeks of recovery in cynomolgus monkeys.

The objective of the non-GLP single-dose study was to evaluate the tolerability and TK profile of lanadelumab when administered once by IV infusion (approximately 10 minutes) to male and female cynomolgus monkey, as well as to evaluate the recovery, persistence, or progression of any effects following a minimum of a 28-day observation period. Lanadelumab (in a vehicle consisting of 30 mM sodium phosphate, 8.6 mM citric acid, 50 mM histidine, 90 mM sodium chloride, pH 6.0, and 0.01% polysorbate 80) was administered as a single IV infusion to cynomolgus monkeys (n=2 per sex per group) at doses of 5, 25, or 50 mg/kg, at a dose volume of 5 mL/kg. Parameters evaluated included mortality and moribundity, clinical observations, detailed physical examinations, body weight, hematology, coagulation, serum chemistry, and urinalysis. Toxicokinetic evaluations were also conducted. All animals survived to the end of the study. There were no lanadelumab-related clinical observations or effects on body weights. Hematology, coagulation, serum chemistry, and urine parameters were unaffected by lanadelumab administration.

Based on the results of this study, a single IV infusion of lanadelumab at dose levels of 5, 25, and 50 mg/kg to cynomolgus monkeys was well tolerated at all dose levels evaluated. A dose of 50 mg/kg corresponded to mean AUClast values of 132000 and 143000 µg·hr/mL and Cmax values of 1300 and 1010 µg/mL for males and females, respectively. In our proposal we will administer a dose of around 5 mg/kg (300 mg).

The objective of a GLP study repeat-dose study was to evaluate the toxicity potential and TK profile of lanadelumab when administered once weekly for 4 weeks by IV infusion (approximately 10 minutes) to male and female cynomolgus monkeys, as well as to evaluate the recovery, persistence, or progression of any effects following a minimum of a 28-day recovery period.

In this study, vehicle (30 mM sodium phosphate, 8.6 mM citric acid, 50 mM histidine, 90 mM sodium chloride, pH 6.0, and 0.01% polysorbate 80) or lanadelumab at doses of 5, 25, or 50 mg/kg was administered via IV infusion once weekly for 4 weeks (Study Days 0, 7, 14, 21, and 28 [5 total doses]) to groups of 5 (Groups 1 and 4) or 3 (Groups 2 and 3) cynomolgus monkeys per sex. Following the final

dose administration, 3 animals per sex per group were euthanized; the remaining 2 animals per sex from Groups 1 and 4 were euthanized following a 28-day recovery period. The dose volume for all groups was 5 mL/kg. Parameters evaluated included mortality and moribundity, clinical examinations, detailed physical examinations, body weight, ophthalmology, ECG, heart rate, blood pressure and respiration rate, hematology, coagulation, serum chemistry, urinalysis, organ weights, and macroscopic and microscopic histological examinations. Toxicokinetic and ADA evaluations were conducted in all animals.

All animals survived to the scheduled necropsies. There were no lanadelumab-related clinical observations or effects on body weights, clinical pathology parameters, ECG parameters, blood pressure, respiration rates, or organ weights. There were no lanadelumab-related ophthalmic, gross, or microscopic findings.

A total of 72 samples collected on Study Days 0, 29, and 57 were screened for the presence of anti-lanadelumab antibodies in cynomolgus monkey sodium citrate plasma. Of these, 7 presumptive positive samples were subjected to confirmatory analysis; 2 of those samples (50 mg/kg male at Study Day 57; and 50 mg/kg female at Study Day 0) were confirmed positive for the presence of anti-lanadelumab antibodies. The control group female did not confirm positive at the subsequent collection (Study Day 29). Presence of ADAs had no impact on exposure in cynomolgus monkey plasma.

Based on the results of this study, once weekly IV infusion (approximately 10 minutes) of lanadelumab at doses of 5, 25, or 50 mg/kg for 4 weeks (Study Days 0, 7, 14, 21, and 28 [5 total doses]) was well tolerated in cynomolgus monkey. There were no adverse lanadelumab-related findings noted at any dose level and the highest dose of 50 mg/kg was determined to be the NOAEL. This dose corresponded to mean Study Day 21 AUClast values of 127000 or 119000 µg·hr/mL and Cmax values of 1650 or 1630 µg/mL, for males and females respectively.

The nonclinical development program for lanadelumab as described in this section and listed in Appendix 2 demonstrate that lanadelumab did not have adverse effects on vital functions or produce adverse target organ pathologies in rats or cynomolgus monkeys at all tested doses.

